# Impact of an integrated nutrition, health, water sanitation and hygiene, psychosocial care and support intervention package delivered during the pre- and peri-conception period and/or during pregnancy and early childhood on linear growth of infants in the first two years of life, birth outcomes and nutritional status of mothers: study protocol of a factorial, individually randomized controlled trial in India

**DOI:** 10.1186/s13063-020-4059-z

**Published:** 2020-01-31

**Keywords:** Pre- and peri-conception, Pre-pregnancy, Stunting, Preterm, Small-for-gestation age, Low birth weight, Integrated intervention, Pregnancy interventions, Nutrition interventions, Growth, Intergenerational effect

## Abstract

**Background:**

The period from conception to two years of life denotes a critical window of opportunity for promoting optimal growth and development of children. Poor nutrition and health in women of reproductive age and during pregnancy can negatively impact birth outcomes and subsequent infant survival, health and growth. Studies to improve birth outcomes and to achieve optimal growth and development in young children have usually tested the effect of standalone interventions in pregnancy and/or the postnatal period. It is not clearly known whether evidence-based interventions in the different domains such as health, nutrition, water sanitation and hygiene (WASH) and psychosocial care, when delivered together have a synergistic effect. Further, the effect of delivery of an intervention package in the pre and peri-conception period is not fully understood. This study was conceived with an aim to understand the impact of an integrated intervention package, delivered across the pre and peri-conception period, through pregnancy and till 24 months of child age on birth outcomes, growth and development in children.

**Methods:**

An individually randomized controlled trial with factorial design is being conducted in urban and peri-urban low- to mid-socioeconomic neighbourhoods in South Delhi, India. 13,500 married women aged 18 to 30 years will be enrolled and randomized to receive either the pre and peri-conception intervention package or routine care (first randomization). Interventions will be delivered until women are confirmed to be pregnant or complete 18 months of follow up. Once pregnancy is confirmed, women are randomized again (second randomization) to receive either the intervention package for pregnancy and postnatal period or to routine care. Newborns will be followed up till 24 months of age. The interventions are delivered through different study teams. Outcome data are collected by an independent outcome ascertainment team.

**Discussion:**

This study will demonstrate the improvement that can be achieved when key factors known to limit child growth and development are addressed together, throughout the continuum from pre and peri-conception until early childhood. The findings will increase our scientific understanding and provide guidance to nutrition programs in low- and middle-income settings.

**Trial registration:**

Clinical Trial Registry – India #CTRI/2017/06/008908; Registered 23 June 2017, http://ctri.nic.in/Clinicaltrials/pmaindet2.php?trialid=19339&EncHid=&userName=society%20for%20applied%20studies

## Background

The major focus of the Millennium Development Goals was on reducing childhood mortality whereas the subsequent Sustainable Development Goals (SDGs) lay emphasis not only on improving survival but also on promotion of overall health and wellbeing of children [1, 2]. Adequate growth and development of the child lays the foundation of adult health and productivity and is an integral step towards achieving the SDGs. Evidence indicates that the first 1000 days of life i.e. from conception to two years of age are critical for optimal growth and brain development [3, 4]. Linear growth and neurodevelopment are particularly interlinked in the first two years of life as the etiology of poor growth (stunting) and neurodevelopment, such as insufficient nutrition, repeated infections and sub-optimal care, are similar during this period [5–7]. Birth weight, gestational age and size at birth are key parameters influencing growth and development in early life [8–10]. Low birth weight (LBW) resulting from both preterm birth and intrauterine growth retardation is a predictor of linear growth in early childhood and an important risk factor for stunting and poor cognitive development, in addition to its substantial contribution to mortality [11–13].

Most studies have tested the effect of standalone interventions within the first 1000 days window; primarily in the domains of health, nutrition, WASH and psychosocial health. These interventions were found to have modest effects on linear growth. The largest impact of a single intervention during pregnancy on birth weights was ~ 50 g mean difference (0.1 standard deviation; SD) and 15% reduction in those born LBW [14, 15]. The impact of a single intervention during pregnancy and/or the postnatal period on attained length was ~ 0.4 cm mean difference (0.1 SD) and ~ 15% reduction in stunting at 24 months of age was seen [16].

Valuable insights for the selection of study interventions were provided by an extensive literature review on interventions that influence birth, growth and development outcomes in children. Firstly, the causes are multifactorial and interventions are needed in the domains of health, nutrition, WASH and psychosocial care and support. Secondly, studies that tested the effect of standalone interventions found modest effects. It is yet uncertain whether the effects are synergistic, if interventions are delivered together as a package. Thirdly, interventions need to be delivered across the critical periods i.e. the 1000-days window from conception to birth and up to 24 months of child age. The review also revealed that the impact of delivering an intervention package covering the four different domains during the pre- and peri-conception period is yet unexplored [17].

Although the 1000 days period is indeed a critical window for the infant, mother’s own health, both physical and mental, as well as her nutrition at the time of conception is important for her own wellbeing and healthy birth outcomes and thriving of her child [18–20]. Poor nutrition in women of reproductive age and during pregnancy can impair fetal growth, which is associated with preterm birth and small-for-gestation (SGA) newborns [21, 22]. Undernutrition and deficiency of micronutrients such as iron, iodine and folic acid in women can have substantial effects on infant health and development outcomes [21, 23]. Hypothyroidism, hypertension and diabetes, and reproductive tract infections (RTI) also affect birth outcomes and subsequent infant survival, health and growth [24–27].

Observational data reveal a relationship between substance use in mothers, specifically of alcohol and tobacco, and maternal depression, with child growth and development [28–30]. The psychosocial health of women at the time of pregnancy may also influence fetal and infant growth [31].

Maternal height is an indicator of intergenerational linkages between maternal and child nutrition and health; short maternal height is associated with offspring undernutrition [32].

We are conducting an individually-randomized controlled trial in urban and peri-urban low- to mid-socioeconomic neighborhoods in Delhi, India to ascertain the impact that can be achieved on birth outcomes, growth and development in children by intervening before women become pregnant, in addition to delivering interventions during pregnancy and postnatal life. The study aims to achieve optimal growth and development in infants and children through concurrent delivery of an integrated package of evidence-based interventions covering the continuum from the pre- and peri-conception period to early childhood. We used a factorial design so that the impact of intervening during the pre-pregnancy period alone could also be assessed.

### Objectives

The primary objective is to determine the effect of integrated and concurrent delivery of interventions to improve health, nutrition, WASH and psychosocial status during the pre- and peri-conception period alone (pre- and peri-conception intervention package); during pregnancy and early childhood (enhanced antenatal, postnatal and early childhood care) and; throughout the pre- and peri-conception period, pregnancy and early childhood (pre- and peri-conception intervention package and enhanced antenatal, postnatal and early childhood care), on preterm birth, LBW and SGA, and stunting at 24 months of age compared to routine care and additionally, to assess whether the effect of these interventions differs by maternal stature (< 150 cm or ≥ 150 cm).

The secondary objectives are to determine the effect of the same package on nutritional status, morbidity and neurodevelopment in children, and on women’s nutritional status and morbidity in the pre- and peri-conception, pregnancy and postpartum periods.

## Methods

### Study design, setting and participants

The study is an individually randomized trial with a factorial design and is being conducted in urban and peri-urban low-to mid-socioeconomic neighborhoods of South Delhi, India [33]. In this setting, the proportion of infants born LBW (~ 25%), the stunting rates among under twos (~ 40%) and maternal undernutrition (body mass index [BMI] < 18.5 kg/m^2^) ~ 22%, are similar to the national average [34].

Eligible women are identified through a door-to-door survey. Those who consent for participation are enrolled (first randomization) and followed up until they are confirmed to be pregnant, or have completed 18 months of follow up post-enrolment. Once pregnancy is confirmed, consent is taken (second randomization) from the women for her and her infant’s participation in the trial (Fig. 1).

**Fig. 1 Fig1:**
[figure not shown]
Study design

### Inclusion criteria

Women aged 18–30 years, married and living with their husband, with no or one child and wish to have a child, and consent for participation in the study.

### Exclusion criteria

Families who plan to move out of the study area or live in temporary housing (households without concrete roof, toilet, water connection and legal electricity) are excluded as they are likely to be relocated by the government in the near future.

### Sample size

Sample sizes were calculated for 90% power and 95% confidence level except for the preterm birth outcome for which the power is 80% for comparison between effect of pre- and peri-conception intervention package and enhanced antenatal, postnatal and early childhood care. Larger effect sizes than those shown for single interventions were assumed for the combined effect of pre- and peri-conception intervention package, enhanced antenatal, postnatal and early childhood care group [14–16]. A 1.5 times higher effect size for the impact of either pre- and peri-conception intervention package or enhanced antenatal, postnatal and early childhood care compared with control, and at least 2 times higher for combined effect of pre- and peri-conception intervention package and enhanced antenatal, postnatal and early childhood care compared to control was assumed (Tables 1 and 2).

**Table 1 Tab1:** Sample size estimates for effect of pre- and peri-conception intervention package alone A + B vs C + D) or Enhanced antenatal, postnatal and early childhood care alone (A + C vs B + D)

	Main effect size	Sample size per two groups
Linear growth at 24 months		
- Mean length-for-age z-score (LAZ)	0.15 SD (absolute value 0.65 cm at 24 mo)	935
- Proportion stunted (30%)	25% relative reduction	772
Birth weight/birth length	0.15 SD (absolute value 75 g birth weight and 0.35 cm birth length)	935
Proportion LBW (25%)	25% relative reduction	918
Preterm birth (12%) [35]	25% relative reduction	2193
SGA at birth (36%) [10]	25% relative reduction	558

90% power and 95% confidence level for all outcomes

**Table 2 Tab2:** Sample size estimates for the combined effect of pre- and peri-conception intervention package and enhanced antenatal, postnatal and early childhood care (A vs D)

	Main effect size	Sample size per group
Linear growth at 24 months		
- Mean LAZ	0.20 SD (absolute value 0.80 cm at 24 mo)	527
- Proportion stunted (30%)	30% relative reduction	491
Birth weight/birth length	0.20 SD (absolute value 100 g birth weight and 0.45 cm birth length)	527
Proportion LBW (25%)	30% relative reduction	624
Preterm birth (12%) [35]	30% relative reduction	1100
SGA at birth (36%) [10]	30% relative reduction	381

90% power for all outcomes except 80% for preterm births. 95% confidence level for all outcomes

We propose to enrol a total of 13,500 eligible women (6750 in pre- and peri-conception intervention package group and 6750 in control group) based on the following assumptions: 45% of reproductive-age women randomized get pregnant in the 18 months of the pre- and peri-conception intervention period, 30% loss (abortions, still births, maternal deaths, moving away, refusals) between pregnancy and live birth and 20% loss (loss-to-follow-up and child deaths) between birth and 24 months of age.

We will get ~ 1100 live births per group. This will enable us to detect a 25% difference in preterm births, proportion LBW and SGA between pre- and peri-conception package alone and control group (A + B vs C + D) and enhanced antenatal, postnatal and early childhood care alone and control group (A + C vs B + D) and a mean difference of 0.15 SD in LAZ score at 24 months for the above comparisons.

We will get at least 600 children in each of the four groups (A, B, C, D) at 24 months. We will be able to detect 0.2 SD difference in mean LAZ score at 24 months and 0.2 SD difference in birth weight and birth length between pre- and peri-conception intervention package and enhanced antenatal, postnatal and early childhood care and control group.

The sample size of ~ 2400 (at least 600 children in each of the 4 groups) at 24 months of age will also allow us to detect an interaction odds ratio (lOR) of ≥1.70 to 1.85 in the proportion of stunted children among short mothers (< 150 cm) and among tall mothers (≥ 150 cm) between the control (routine care) and the intervention group who received the intervention package throughout, with 80% power and 95% confidence level.

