### Statistical analyses

#### Primary comparisons

The primary analysis will be factorial, for comparison of the pre- and peri-conception intervention package (pre- and peri-conception intervention package alone or with enhanced antenatal, postnatal and early childhood care package i.e. Group A + B) with no pre- and peri-conception intervention package (enhanced antenatal, postnatal and early childhood care package alone or routine care i.e. Group C + D), and the enhanced antenatal, postnatal and early childhood care (with pre- and peri-conception intervention package or enhanced antenatal, postnatal and early childhood care alone i.e. Group A + C) with no enhanced antenatal, postnatal and early childhood care (pre- and peri-conception intervention package alone or routine care i.e. Group B + D) on birth outcomes (mean birth weight and length, proportion stunted at birth, proportion of babies born preterm and spontaneous preterm births, SGA and LBW) and mean length for age z-score and proportion stunted at 24 months.

In addition to the factorial analysis, we will also examine the impact of the combined pre- and peri-conception intervention package and enhanced antenatal, postnatal and early childhood care (Group A) on birth outcomes and attained length at 24 months of age, compared to routine care (Group D).

We will examine if there is an interaction between the intervention package delivered during peri-preconception period and that delivered during antenatal and early childhood period on primary outcomes.

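### The effects assumed in Tables 1 and 2 do not fit one set of four group means: 0.15 SD on each factorial margin implies 0.30 SD for A vs D, but Table 2 plans on 0.20 SD

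*Protocol article*

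**What the plan says.** All references are to the protocol article; A is both packages, B the pre-conception package only, C the pregnancy and childhood package only, and D routine care.

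- **Sample size, first paragraph.** Effects are scaled up from those of single interventions: "A 1.5 times higher effect size for the impact of either pre- and peri-conception intervention package or enhanced antenatal, postnatal and early childhood care" relative to control, and "at least 2 times higher for combined effect" of the two packages. The Background gives the single-intervention reference as about 0.1 SD for birth weight and for attained length, so the multiples are 0.15 SD and 0.20 SD.
- **Table 1.** The contrasts are A+B vs C+D and A+C vs B+D, captioned as the effect of each package *alone*. The LAZ row reads "0.15 SD (absolute value 0.65 cm at 24 mo", with 935 per pooled side; the binary rows use a 25% relative reduction. The footnote states "90% power and 95% confidence level for all outcomes".
- **Table 2.** For A vs D the LAZ row reads "0.20 SD (absolute value 0.80 cm at 24 mo", with 527 per group; the binary rows use 30%. The footnote states "90% power for all outcomes except 80% for preterm births".
- **Sample size, text after the tables.** About 1,100 live births per group and at least 600 children per group at 24 months are expected. These are said to allow detection of 25% differences in the birth outcomes and "a mean difference of 0.15 SD in LAZ score at 24 months for the above comparisons", meaning the pooled contrasts.
- **Primary comparisons.** "The primary analysis will be factorial"; A vs D and the interaction are examined in addition.

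**The concern.** The 1.5-times effect is described as either package against control and is labelled *alone*. That describes a simple effect (B vs D, or C vs D), yet Table 1 uses it as the size of a pooled margin. A margin averages the effect of a package without the other one and its effect on top of the other one. If the two packages together give only 0.20 SD, the second average component is small and the margin is smaller than 0.15 SD.

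The factorial margins are the primary analysis, and the Discussion counts adequate power for the pre-conception question among the trial's strengths. If the combined effect is what Table 2 assumes, a non-significant margin for preterm birth, LAZ or stunting would be judged against 90% power that the trial does not have for those outcomes.

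**Working it through.** **1. Reproducing the plan.** Two-sided 5% is assumed (sidedness is not stated). For means, n = 2(1.960 + 1.282)²/d².

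- d = 0.15: 934 (stated 935). d = 0.20: 526 (stated 527).
- For proportions with pooled variance and no continuity correction, Table 1 gives LBW 918, preterm 2,193 and SGA 558, all as stated. Stunting gives 722 against the stated 772, a separate matter that does not affect this point.

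So the formulas are confirmed, and Table 1's sizes are per pooled side.

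**2. The identity.** With equal groups, where each letter is a group mean or risk:

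[(A+B)/2 − (C+D)/2] + [(A+C)/2 − (B+D)/2] = A − D.

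B and C cancel, so this holds whatever the interaction.

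- Means: 0.15 + 0.15 = 0.30 SD for A−D; Table 2 has 0.20 SD.
- Risk differences at Table 1's control rates: stunting 2 × 0.25 × 0.30 = 0.15, Table 2 has 0.30 × 0.30 = 0.09; LBW 0.125 vs 0.075; preterm 0.06 vs 0.036; SGA 0.18 vs 0.108.

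**3. Factorial effects if Table 2 is taken as it stands.**

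- Means: the two margins average 0.20/2 = 0.10 SD. With D = 0, B = C = 0.15 and A = 0.20, each margin is (0.20 + 0.15)/2 − (0.15 + 0)/2 = 0.10 SD.
- Risks: with D = p, B = C = 0.75p and A = 0.70p, the margins are 0.725p and 0.875p. The ratio is 0.829, a reduction of about 17%. Splitting the 30% multiplicatively instead gives √0.70 = 0.837, about 16%.

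**4. Expected numbers per margin.**

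- Stated: 2 × 1,100 = 2,200 births and 2 × 600 = 1,200 children.
- From the plan's own rates: 13,500 × 0.45 × 0.70 = 4,252 births, or about 2,126 per margin; × 0.80 = 3,402 children, or about 1,701 per margin (about 850 per group).

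**5. Power in that scenario.** For means, power = Φ(0.10√(n/2) − 1.96); for proportions, the same pooled-variance method as in step 1.

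| Outcome | Margins | At Table 1 size | At expected numbers | n per margin for 90% |
|---|---|---|---|---|
| Birth weight, length | 0.10 SD | 58% (935) | 90% (2,126), 91% (2,200) | 2,102 |
| LAZ, 24 months | 0.10 SD | 58% (935) | 69% (1,200), 83% (1,701) | 2,102 |
| Stunting, 24 months | 21.75% vs 26.25% | 54% (772) | 73% (1,200), 87% (1,701) | 1,891 |
| LBW | 18.1% vs 21.9% | 52% (918) | 86% (2,126), 88% (2,200) | 2,389 |
| Preterm birth | 8.7% vs 10.5% | 53% (2,193) | 51% (2,126), 53% (2,200) | 5,627 |
| SGA | 26.1% vs 31.5% | 51% (558) | 97% (2,126), 98% (2,200) | 1,476 |

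**6. The opposite resolution.** If 0.15 SD per margin is right, A−D is 0.30 SD and needs 234 per group for 90% power, so 527 is more than enough.

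**7. The detection statements.** A 0.15 SD margin has 96% power at 1,200 per margin. A 25% reduction in preterm birth (12% vs 9%) has 89% at 2,126 and 90% at 2,200.

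**The case against.** The strongest reply is that the combined effect is given as a floor. A value of 0.30 SD satisfies it, and minimum detectable differences for two different contrasts need not add up. On that reading Table 1's power stands and Table 2 is merely conservative. In support, the text after the tables speaks of differences the trial can detect, and as such those figures are essentially correct (step 7). They need qualifying, not correcting.

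This reply limits the point but does not remove it. The first paragraph says the effects were assumed, both tables come from one set of multiples, and Table 2 and the later text both use 0.20 SD. Nowhere does the protocol say that Table 1 needs three times the single-intervention effect for A vs D.

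A second reply is that the document never gives B−D or C−D as numbers, and that control may mean the pooled comparison side. That is fair. Without those values, only the average of the two margins (0.10 SD) follows, and only if A−D is exactly 0.20 SD.

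A reader might also infer from the third column of the table that the trial has only 51–58% power for its primary analysis. The documents do not support this. Those figures hold at Table 1's minimum sizes, and for most outcomes the trial expects clearly more births or children. Nor does it follow that 527 is wrong; a size set for a minimum effect is valid for that effect.

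**Conclusion.** As assumed effects, Tables 1 and 2 contradict each other: 0.15 SD on both margins requires 0.30 SD for A vs D, and Table 2 plans on 0.20 SD. This rests only on equal group sizes. The loss of power is conditional on the combined effect being no larger than Table 2's 0.20 SD or 30% and, for the binary outcomes, on each package alone giving 25% (a multiplicative split changes little).

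Under that condition the shortfall at expected numbers is severe for preterm birth. For LAZ and stunting it is material at 600 children per group and modest at about 850. For LBW it is slight. Birth weight, birth length and SGA are adequately powered. The stated power basis for the primary analysis should be restated, but the design itself does not fail.

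**What to change.** Derive both tables from one explicit set of four group means or risks, in one of two ways:

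1. Keep A−D at 0.20 SD and 30%. Restate the Table 1 factorial effects as about 0.10 SD and 17%, and report the power that the expected births and children give for each outcome.
2. Keep 0.15 SD per margin. State that this implies 0.30 SD for A vs D, so that 527 per group in Table 2 is a conservative size for a minimum effect. Give the binary rows the same treatment.

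In either case, add to the text after the tables that 0.15 SD and 25% are detectable differences on the pooled margins, and that they exceed the margins implied by a combined effect of 0.20 SD or 30%.

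The cost is recalculated table entries and a few sentences. Enrolment, data collection and the planned analyses do not change; the one drawback is that the stated power is less favourable under the first option.

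### Table 1 gives 772 for stunting, but its own inputs give 722; every other row of the table reproduces

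*Protocol article*

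**What the plan says.** In the protocol article, Sample size, Table 1 covers the two factorial comparisons (A + B vs C + D, and A + C vs B + D). Its last column is headed "Sample size per two groups", that is, the number on each side of the pooled comparison. The stunting row, "Proportion stunted (30" per cent, assumes a "25% relative reduction" and gives 772.

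The other binary rows use the same relative reduction:

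- "Proportion LBW (25" per cent: 918
- "Preterm birth (12%) [35": 2193
- "SGA at birth (36%) [10": 558

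The two rows for continuous outcomes assume 0.15 SD and each give 935. The footnote states "90% power and 95% confidence level for all outcomes". No row has its own formula, continuity correction or inflation factor.

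**The concern.** The stunting row prints everything needed to compute its sample size, and the result differs from the printed figure. Stunting at 24 months is a primary outcome and part of the primary factorial analysis, so this row is where a reader would check the justification for that comparison. Reaching 772 would take a control proportion of about 28.5% or a relative reduction of about 24.2%. Neither is stated, and both contradict the row itself. As printed, the reader cannot be sure whether the number or one of its inputs is wrong.

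**Working it through.** **Inputs**

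- Control proportion p1 = 0.30 and relative reduction 25% (Table 1), so p2 = 0.30 × 0.75 = 0.225.
- Power 90% and 95% confidence (Table 1 footnote). Sidedness is not stated. I take a two-sided 5% test, because the other binary rows reproduce that way and not one-sided. So z = 1.96 and 1.2816.
- Equal allocation, from the enrolment split "6750 in pre- and peri-conception intervention package group and 6750 in control group".

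**Formula** (pooled variance under the null, p̄ = (p1 + p2)/2)

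n per side = [1.96 √(2 p̄(1 − p̄)) + 1.2816 √(p1(1 − p1) + p2(1 − p2))]² / (p1 − p2)²

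**Check on the other rows.** The article does not name its formula, so I first tested this one against the rest of the tables, rounding up.

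| Row | p1 → p2 | Computed | Printed |
|---|---|---|---|
| Table 1, LBW | 0.25 → 0.1875 | 917.3 → 918 | 918 |
| Table 1, preterm | 0.12 → 0.09 | 2192.2 → 2193 | 2193 |
| Table 1, SGA | 0.36 → 0.27 | 557.7 → 558 | 558 |
| Table 2, stunting | 0.30 → 0.21 | 490.8 → 491 | 491 |
| Table 2, LBW | 0.25 → 0.175 | 623.1 → 624 | 624 |
| Table 2, SGA | 0.36 → 0.252 | 380.5 → 381 | 381 |

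The Table 2 preterm row, at its stated 80% power, computes to 1109 against 1100 printed, a difference under 1%. For the continuous outcomes, 2(1.96 + 1.2816)²/0.15² gives 934 by the normal approximation; the t-test version gives the printed 935, and likewise 527 for 0.20 SD in Table 2.

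**The stunting row of Table 1**

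- p̄ = 0.2625
- First term: 1.96 × √(2 × 0.2625 × 0.7375) = 1.2196
- Second term: 1.2816 × √(0.21 + 0.174375) = 0.7945
- n = (1.2196 + 0.7945)² / 0.075² = 721.2, so **722**, against 772 printed

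**Could another method explain 772?**

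| Variant | n per side |
|---|---|
| Unpooled variance | 718 |
| Arcsine | 720 |
| Pooled variance in both terms | 723 |
| Log odds ratio | 727 |
| Log relative risk | 734 |
| Continuity correction | 748 |
| One-sided 5% | 588 (614 with continuity correction) |
| 80% power | 540 (566 with continuity correction) |
| 722 inflated for 20% loss, 722/0.8 | 903 |

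None gives 772. Continuity correction would also change the LBW, preterm and SGA rows to 950, 2259 and 580, which are not the printed values.

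**Size**

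- 772 − 722 = 50 per side, and 50/722 = 6.9%.
- Power with the stated inputs is 90.0% at 722 and 91.8% at 772.
- The protocol expects at least 600 children per group at 24 months, so 2 × 600 = 1200 per pooled side. Power there is about 98.7%.

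**The case against.** The strongest reply is that nothing rests on this cell. Enrolment of 13,500 is built from pregnancy and loss rates. The largest requirement in the table is preterm birth at 2193. The 1200 or more children expected per pooled side at 24 months exceed 722, 772 and the 935 for length-for-age. The text listing the detectable main effects names preterm birth, LBW, SGA and length-for-age, but not stunting. The figure also errs on the safe side. And since 30% reproduces Table 2 and 25% reproduces three other rows of Table 1, the likeliest explanation is one mistyped digit rather than an undisclosed input.

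All of this stands as a limit on importance. It does not rescue the figure: 772 still contradicts the inputs printed beside it. The typing error is an inference that only the authors can confirm.

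**Conclusion.** The concern holds. The Table 1 sample size for stunting should be 722 on its stated inputs, not 772, an overstatement of 50 children per side or about 7%. It is the only row of Table 1 that does not reproduce. The conclusion assumes a two-sided 5% test, equal allocation and the pooled-variance formula. The article states neither sidedness nor formula, but the other binary rows of Table 1 match to the unit under these assumptions, and none of the usual alternatives gives 772. The matter is minor: the error is conservative, it is not the binding requirement, and no power claim or enrolment target changes.

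**What to change.** Correct 772 to 722 in the stunting row of Table 1. If 772 was intended, state the control proportion or relative reduction that produces it. Naming the formula and sidedness under the table would let a reader check every row. The cost is one number, or one sentence, with no effect on enrolment, conduct or analysis.

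### The detectable stature interaction odds ratio of 1.70 to 1.85 is stated for A vs D but fits all 2400 children; with 600 per group it cannot fall below 1.91

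*Protocol article*

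**What the plan says.** The protocol article, Sample size, gives the expected yield as "We will get at least 600 children in each of the four groups (A, B, C, D) at 24 months". It then makes a power statement for effect modification by maternal height. The basis is "The sample size of ~ 2400 (at least 600 children in each of the 4 groups) at 24 months of age", and the claim is that this suffices to "detect an interaction odds ratio (lOR) of ≥1.70 to 1.85 in the proportion of stunted children among short mothers (< 150 cm") and among taller mothers. The comparison is "between the control (routine care) and the intervention group who received the intervention package throughout", "with 80% power and 95% confidence level".

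The Objectives section places this question within the primary objective: the trial is additionally "to assess whether the effect of these interventions differs by maternal stature", with the cut at 150 cm. Randomization is stratified at the same cut. Table 2 gives the planning rates for A vs D: 30% stunted under routine care and a 30% relative reduction. The article does not give the share of mothers under 150 cm or the stunting rates assumed for the interaction calculation.

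**The concern.** The sentence counts children in all four groups but names a comparison that uses two. Groups B and C add nothing to a direct A vs D contrast, so the information available is about half of what the quoted total suggests. An interaction is already estimated much less precisely than a main effect, so halving the sample matters.

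The stature question belongs to the primary objective, and the Discussion presents it as a strength of the design. If the true interaction odds ratio lay between 1.70 and 1.85, the trial would have far less than the stated 80% chance of detecting it. A reader who relies on the stated power could then take a non-significant interaction as better evidence of no effect modification than it is.

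**Working it through.** **Inputs from the article.** At least 600 children per group at 24 months; 80% power; 95% confidence; stunting 30% with a 30% relative reduction, so 30% vs 21% (Table 2); about 40% stunting among under-twos in this setting (Study design, setting and participants); attrition assumptions (Sample size). **Assumed.** The share s of mothers under 150 cm, shown from 50% down to 20%.

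**Is alpha two-sided?** Table 2 shows that it is. For stunting at 90% power with two-sided 5%:
n = [1.960·√(2·0.255·0.745) + 1.282·√(0.30·0.70 + 0.21·0.79)]² / 0.09² = 491, the printed value.
For LAZ: n = 2·(1.960 + 1.282)² / 0.20² = 526, against 527 printed.

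**Formula.** For n children per arm,
Var(log IOR) = Σ 1/(n_cell·p·(1−p)) over the four arm-by-stature cells,
detectable IOR = exp[(1.960 + 0.842)·√Var].

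**Floor at 600 per group.** Each term is smallest when p = 0.5, and the sum is smallest when half the mothers are short (300 per cell). Then Var = 4/(300·0.25) = 4/75 = 0.0533, SE = 0.231, and the detectable IOR = exp(2.802·0.231) = 1.91. No other rates or shares give a lower value.

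**Table 2 rates, 600 per group.** With the same rates in both stature strata, Var = [1/(600s) + 1/(600(1−s))]·[1/0.21 + 1/(0.21·0.79)]. The last bracket is 4.76 + 6.03 = 10.79.

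| Share short | SE | Detectable IOR | Power at 1.70 | Power at 1.85 |
|---|---|---|---|---|
| 50% | 0.268 | 2.12 | 51% | 63% |
| 40% | 0.274 | 2.15 | 49% | 61% |
| 30% | 0.293 | 2.27 | 44% | 56% |
| 20% | 0.335 | 2.56 | 35% | 45% |

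Power is Φ(ln IOR/SE − 1.960). With 40% vs 28% stunted, the detectable IOR runs from 2.00 (50% short) to 2.37 (20% short).

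**If retention follows the protocol's assumptions.** 13,500 × 0.45 × 0.70 × 0.80 / 4 = about 850 per group.
- Floor: Var = 4/(425·0.25), SE = 0.194, IOR = 1.72.
- 30% vs 21%: 1.88 (50% short) to 2.20 (20% short).
- 40% vs 28%: 1.79 (50%), 1.81 (40%), 1.88 (30%), 2.07 (20%).

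**What reproduces the printed range.** Splitting all 2400 children as 1200 vs 1200, at 30% vs 21%, gives 1.70 (50% short), 1.72 (40%), 1.79 (30%) and 1.85 (25%). Both printed limits appear. At the margin effect in Table 1 (30% vs 22.5%), the last bracket becomes 1/0.21 + 1/(0.225·0.775) = 10.50, and the values are 1.69 (50% short) to 1.83 (25% short).

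**The case against.** **The 600 is a floor.** The article says at least 600, and its own attrition figures give about 850. This stands in part. At 850 the bound drops to 1.72, and with 40% vs 28% stunted and 40% to 50% of mothers short the detectable value (1.79 to 1.81) lies inside the printed range. A reader might infer that the range is out of reach however many children are retained; the article's figures do not support that. They do not rescue the sentence either. It rests on 600 per group and a total of about 2400, the Table 2 rates still give 1.88 or more at 850, and 1.70 is never reached.

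**The true figure is unknown.** A reader might take 2.12 to 2.56 as the correct value. It is not one that the article fixes, because the share of short mothers is assumed. At 15% short it would be 2.86, and it also moves if stunting differs by stature. Only the 1.91 bound is free of such assumptions.

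**A different test or model.** A one-sided 5% test lowers the bound at 600 only to 1.78, and Table 2 uses two-sided alpha. An additive four-group factorial model does not help: A minus D is then the sum of the two factor effects, with the same variance as the direct contrast.

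**Little depends on it.** The enrolment target is not shown to rest on this figure; Table 2's A vs D sizes for LAZ (527) and stunting (491) fit within 600. The article lists the stature analysis among several subgroup analyses and attaches no decision rule to it. All of this stands. It limits the consequence but does not make the printed power correct.

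**Conclusion.** The power statement is wrong as written. For A vs D with 600 children per group, a two-sided 5% test and 80% power, an interaction odds ratio of 1.70 to 1.85 is not detectable under any stunting rates or share of short mothers. Real power there, at Table 2 rates and 20% to 50% short, is roughly 35% to 63%. The printed range agrees closely with a calculation that uses all 2400 children as two halves. That is the likely origin, but it is an inference, since the article does not show its calculation.

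A reader might go further and conclude that the trial is too small for its primary outcomes. This point does not show that. It concerns the stated power for effect modification by stature in one contrast, and leaves the main-effect sample sizes as they are.

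**What to change.** Correct the sentence in one of two ways, and in either case state the assumed share of mothers under 150 cm and the stunting rates.

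1. Keep A vs D and restate the detectable interaction odds ratio for the number of children relied on. For shares of 50% down to 20% this is 2.12 to 2.56 at 600 per group or 1.88 to 2.20 at about 850, with 30% vs 21% stunted. With 40% vs 28% it is 2.00 to 2.37 or 1.79 to 2.07.
2. Attach 1.70 to 1.85 to the factorial margins, A+B vs C+D and A+C vs B+D, where about 1200 vs 1200 children support it if roughly 25% to 50% of mothers are short. The Objectives do not confine the stature question to A vs D, so this analysis is already open. The text should say that it asks whether stature modifies each package separately, which is a different question from the combined package against routine care.

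The cost is one revised sentence, with no extra enrolment or data collection.
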